#### Predictive modelling of heterogeneous effects

We will estimate individual-level prediction models of the primary and secondary outcomes given allocation to the enhanced tailored intervention,^28 76^ personalised intervention and control. From these predictions, we will estimate the individual-level effects of the interventions, which will allow us to explore which individuals, defined by their baseline characteristics and interactions in the interventions, are more or less likely to benefit.

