Furthermore, an intervention can be tailored to match an individual’s readiness to change their drinking behaviour. Process of change models, such as the Transtheoretical Model^47^ or the Health Action Process Approach,^48^ point towards a continuum of change an individual will iteratively progress through before a longer-term change in behaviour is established and maintained. These models present a valuable framework for designing and implementing health behaviour change interventions that can be tailored to meet individual needs and in turn result in greater effectiveness. For example, a brief intervention may be ineffective if the individual is not ready to change. However, if the content is tailored to target and address ambivalence for change, it may meet the individual’s specific needs for facilitating change.^47^

In this study, we will investigate a digital alcohol intervention tailored to individuals’ motives for drinking and readiness to change. The primary aim of the study is to estimate the intervention’s effectiveness in terms of weekly alcohol consumption and frequency of heavy episodic drinking among Swedish adults who are looking for help online. The enhanced tailored intervention will be contrasted against two comparators: (1) the existing personalised intervention, which was previously found to be effective,^16^ and (2) referral to online resources that would typically be found when looking online. Secondary aims of the study include estimating the degree to which the effects of the interventions are mediated through mechanisms of behaviour change and estimating individual-level effects.

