### Interventions

#### Control group

Participants allocated to online support materials will be referred to two national websites with information about alcohol and health (ie, 1177.se and IQ.se). They will be instructed to read these materials and use any available support. They will also be informed that we will contact them again to conduct follow-up surveys. At the end of trial participation, 8 months postrandomisation, control group participants will receive the personalised intervention which has been shown to be effective.^16^

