#### Personalised intervention group

Participants allocated to the personalised intervention will be given immediate access to a digital alcohol intervention for 16 weeks which provides personalised feedback based on the individual’s current consumption in contrast to national guidelines and compared with average consumption levels in the same sex and age group. Notably, this intervention is not tailored for drinking motives or readiness to change, but based on social cognitive theories of health behaviour.^51^ The digital alcohol intervention targets improving motivation and self-efficacy, as well as teaching new skills and addressing environmental constraints—which are understood to improve the likelihood of successful behaviour change,^52^ including for changing one’s drinking.

The core element of the intervention is a text message sent each Sunday afternoon acting as a proactive reminder to engage in the intervention materials. The message includes a prompt to self-monitor current alcohol consumption and a link to a web-based screening tool. The screening tool assesses the past week’s consumption, and participants are subsequently given access to a toolbox with modules containing advice for behaviour change. The content of these modules is anchored in state-of-the-art empirical evidence for which active ingredients are effective for supporting reduced alcohol consumption, including behaviour substitution, problem-solving, goal setting, review of behavioural goals, self-monitoring, normative feedback and understanding the consequences of alcohol consumption.^53 54^

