#### Enhanced tailored intervention group

Participants allocated to the enhanced tailored intervention group will for 16 weeks receive an intervention that follows the same logic as the personalised intervention. The key difference between the two is that after the weekly self-monitoring and feedback on current consumption, participants will be given tailored exercises and advice for behaviour change which have been selected based on the participant’s drinking motives and readiness to change. Periodically, participants in the tailored intervention group will be asked to reassess their readiness to change and motives, using the readiness to change questionnaire (treatment version)^55 56^ and the drinking motives questionnaire (short form).^57^ Matching will be based on the latest available data for participants concerning motives for drinking and readiness to change. Participants who have not progressed to the action stage after 8 weeks will nonetheless receive content related to the action category of readiness to change for the following 4 weeks. The rationale for this is that if no progress has been produced from the precontemplation and contemplation content, then providing something new may be more appropriate. Notable is that the precontemplation and contemplation materials are still available. Weeks 13 through 16 are then again tailored to readiness to change. Online supplemental Appendix C contains details of the enhanced tailored intervention and the reassessment schedule.

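### Who benefits is to be explored partly by participants' use of the intervention, a post-randomisation variable that can produce apparent heterogeneity against control

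*Protocol article*

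**What the plan says.** The section on predictive modelling of heterogeneous effects describes two steps. Prediction models for the primary and secondary outcomes are estimated given allocation to enhanced, personalised or control. Then "From these predictions, we will estimate the individual-level effects of the interventions", with the stated purpose to "explore which individuals, defined by their baseline characteristics and interactions in the interventions, are more or less likely to benefit". The Introduction gives this the status of a secondary aim: the effects "mediated through mechanisms of behaviour change and estimating individual-level effects" are named there together.

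Four other places bear on what use means in each arm:

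- Personalised intervention group: "Participants allocated to the personalised intervention will be given immediate access to a digital alcohol intervention for 16 weeks". Use therefore accrues after allocation and overlaps the 2- and 4-month follow-ups given in Participant timeline.
- Same section: "The screening tool assesses the past week’s consumption, and participants are subsequently given access to a toolbox with modules". Records of use are generated alongside self-reported drinking.
- Control group: "Participants allocated to online support materials will be referred to two national websites with information about alcohol and health". Controls receive the personalised intervention only when trial participation ends at 8 months.
- Enhanced tailored intervention group: the weekly logic is shared with the personalised arm, but exercises are tailored and "Periodically, participants in the tailored intervention group will be asked to reassess their readiness to change and motives". Use is thus partly the same variable in the two active arms and partly not.

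**The concern.** An individual effect compares the same person under two allocations. Whatever defines that person has to be fixed before allocation, or at least exist under both allocations. Use does not qualify for a contrast with control, because the control-side prediction for a heavy user cannot be conditioned on something controls do not have.

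If the intervention-side prediction does condition on use, and use carries information about prognosis or early response that the baseline covariates miss, that information enters one side of the contrast only and appears as a difference in benefit. The report could then say that engaged participants gain and disengaged ones do not, or are even harmed, when the effect is the same for all. In a trial whose premise is fitting support to the individual, readers will take such a statement seriously.

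The section names no method for a post-randomisation variable. The causal framework under Models for mediators covers only the listed mediators (confidence, knowledge and two kinds of norms), and use is not among them.

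**Working it through.** The article states no figure for this analysis, so there is none to reproduce. The checks below show the mechanism and its possible size.

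**1. Closed-form illustration, intervention versus control.**

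Input related to the article: IRR 0.85, corresponding to the 15% difference in weekly consumption used in the sample-size simulations, here held constant for every participant. Assumed inputs, absent from the article: use correlates with a lower residual log outcome at r = 0.2 or 0.3, and the residual SD of the log outcome is 0.6 or 0.8.

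The use slope applies to the intervention side only:

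apparent IRR at ±1 SD of use = exp(ln 0.85 ∓ r × SD) = 0.85 × exp(∓ r × SD)

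| r | SD | r × SD | +1 SD of use | −1 SD of use |
|---|---|---|---|---|
| 0.2 | 0.6 | 0.12 | 0.75 | 0.96 |
| 0.2 | 0.8 | 0.16 | 0.72 | 1.00 |
| 0.3 | 0.6 | 0.18 | 0.71 | 1.02 |
| 0.3 | 0.8 | 0.24 | 0.67 | 1.08 |

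Because the true IRR was set to 0.85 for everyone, the whole spread in this table is artefact. That follows from the assumption and is not a finding about the trial.

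**2. Enhanced versus personalised.**

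Use exists on both sides, so only the difference in slopes remains: 0.85 × exp(∓ difference in r × SD).

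- Equal slopes: the difference is 0, and the result is 0.85 at both +1 SD and −1 SD.
- Slopes of 0.24 (enhanced) and 0.12 (personalised): the difference is 0.12, giving 0.75 and 0.96.

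**3. Simulation of the contrast with control.**

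The outcome was negative binomial, as in the article's primary models. Arm sizes were 583 and 733 (1750/3 and 2200/3, from the anticipated total). Assumptions: mean 12 drinks, dispersion 0.8, one measured baseline covariate, one unmeasured prognostic factor, the same effect for everyone, and no causal effect of use. Use was correlated at rho with the unmeasured factor, with better prognosis meaning more use. The intervention model contained baseline and use; the control model contained baseline only. There were 300 repetitions per setting. Average apparent IRR by third of use:

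| rho | True 0.85: lowest third | True 0.85: highest third | True 1.00: lowest third | True 1.00: highest third |
|---|---|---|---|---|
| 0 | 0.85 | 0.85–0.86 | 1.00–1.01 | 1.00 |
| 0.2 | about 0.95 | 0.76 | 1.10–1.12 | 0.89–0.90 |
| 0.4 | 1.03–1.04 | 0.67 | 1.22–1.24 | 0.80 |
| 0.6 | about 1.13 | 0.59 | 1.33 | 0.69 |

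The coefficient for use passed |z| > 1.96 in 6–9% of runs at rho 0, in 59–70% at rho 0.2, and in 99–100% at rho 0.4 or more. Rho here is the correlation with one unmeasured factor, so it is not the same quantity as r in step 1.

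**4. Same data, baseline-only models on both sides.**

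The lowest and highest thirds of use then both show about 0.85–0.86 (true 0.85) or about 1.00–1.01 (true 1.00) at every rho. The gradient disappears.

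**The case against.** The strongest reply is that the section does not say use enters the prediction models. The models are fitted given allocation, with no covariate list. If they contain baseline variables only and use merely describes participants afterwards, step 4 shows no spurious gradient. The covariates may be settled in an analysis plan that is not shown. This stands: the sentence permits the biased implementation but does not commit the trial to it.

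Three further points also stand.

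- The artefact requires use to be related to residual prognosis; at rho 0 there is none. A reader might infer that the heaviest users are people who would have cut down anyway, but the article does not say so. If struggling drinkers used the tools more, the pattern would reverse.
- The two active arms share weekly self-monitoring and feedback, so use is not wholly different between them. With equal slopes the enhanced-versus-personalised contrast is undistorted in the formula.
- The stated purpose is to explore. Use is unknown when support is assigned, but the article nowhere proposes choosing support from these predictions, so that is no charge against it.

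One could also read the phrase as meaning statistical interaction terms. That is less natural, because it is listed beside baseline characteristics as something that defines individuals, and a model term does not do that.

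The reply does not remove the fault in the sentence itself. It names a post-randomisation variable as part of what defines who benefits, and nothing elsewhere in the article limits how that variable may be used.

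**Conclusion.** The point holds conditionally. Contrasts with control will show heterogeneity by use under a constant effect if two conditions are met: use enters the individual-effect models, and use is related to prognosis or early response beyond the baseline covariates. The second is plausible because the weekly drinking report opens the modules, but the article does not quantify it.

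Under the declared assumptions, the apparent IRR against control runs from 0.67–0.75 at +1 SD of use to 0.96–1.08 at −1 SD, around a true 0.85. These sizes do not carry over to enhanced versus personalised, where only a difference in slopes matters.

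A reader might infer that the plan is bound to report false heterogeneity, or that the trial's main conclusions are at risk. The documents support neither. The model covariates are not fixed, and the intention-to-treat contrasts, the primary models and the recruitment criteria do not involve use. Severity is moderate: this is an exploratory analysis under a secondary aim.

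**What to change.** State that the individual-effect models, and the characteristics used to describe who benefits, are limited for all three allocations to variables measured before randomisation: baseline drinking, demographics, and any mediators, motives or readiness scores collected at baseline in every arm. Remove use of the intervention from the sentence on who benefits. Report it separately, within each active arm, as an association with outcome and not as an effect.

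A principal-stratum analysis of use can be offered as an option. If use is predicted from baseline covariates, that analysis rests on principal ignorability, meaning that no unmeasured prognosis is linked to use once baseline is accounted for. This is the condition in doubt here, so the assumption should be stated alongside any such result.

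The cost is a few words in the article and matching text in the analysis plan, with no new data. The price is that no causal statement about effect by engagement can be made from these models.

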#### Ancillary analyses

We will conduct two attrition analyses. First, if data is missing systematically, then it may be the case that early responders differ from non-responders, and in extension that late responders are more alike non-responders. Therefore, one attrition analysis will regress primary outcomes against the number of attempts to collect follow-up before a response was recorded. Second, we will estimate a logistic regression model with response versus no response regressed against baseline variables with interactions for group allocation. In this second model, we will use shrinkage priors to account for the excessive number of parameters.^77^

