**Trial registration number:**

The trial was preregistered in the ISRCTN Registry on 12 June 2024 (ISRCTN87600318).

STRENGTHS AND LIMITATIONS OF THIS STUDYDouble-blind randomised design enables valid estimation of effects for an intervention tailored to match personal dimensions of behaviour for alcohol outcomes.The use of a Bayesian sequential design will ensure that the trial will not be underpowered or recruit more participants than necessary.Self-report measures will be used which may bias estimates due to social desirability and recall.Mediators will be assessed using single, face-valid items in lieu of validated questionnaires to reduce participant burden.

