### Outcomes

For primary and secondary outcomes, we will use the international consensus-driven core outcome set for brief alcohol interventions,^18^ measured using the recommended questionnaire items.^58^ All questionnaires will be completed by participants on their mobile phones and initiated by sending a text message with a link to the questionnaires (see online supplemental Appendix B for all questionnaires used).

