### Participant timeline

In figure 1, a SPIRIT figure depicts the trial timeline. At 2 and 4 months postrandomisation, primary and mediator outcomes will be assessed to estimate the effects of immediate exposure and prolonged exposure to the interventions. The 4-month follow-up will also include a user evaluation questionnaire. At 8 months postrandomisation, all outcomes will be measured to estimate the persistent effects of the interventions. Up to three reminder texts will be sent at each follow-up interval, followed by phone calls to collect data from those not responding (maximum of five attempts).

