### Allocation and blinding

The backend server will automatically randomise participants to the three groups, post eligibility screening. Block randomisation will be used with random block sizes of 3 and 6. Since all randomisation procedures will be computerised, allocation will be unbiased and research personnel will be blind to allocation. There is a risk that allocation will be revealed to research personnel for some participants during follow-up phone calls. The study information will inform participants that the trial is investigating digital support materials and that they will be randomised to receive different materials. In this way, participants will be blind to allocation since they are unaware of both how many groups there are and what the different groups will receive.

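### The attrition analysis on number of contact attempts cannot separate late response from the move from web link to phone call, so its association needs to be shown within collection mode

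*Protocol article*

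**What the plan says.** Under *Ancillary analyses*, the protocol article describes two attrition analyses. In the first, "one attrition analysis will regress primary outcomes against the number of attempts to collect follow-up before a response was recorded". The reasoning is conditional: if data are missing systematically, it may be that "late responders are more alike non-responders". The second is a logistic regression of response on baseline variables, with interactions for allocation.

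The contact sequence is under *Participant timeline*: "Up to three reminder texts will be sent at each follow-up interval, followed by phone calls to collect data from those not responding", with a limit of five attempts. Under *Outcomes*, the usual route is a web form: "All questionnaires will be completed by participants on their mobile phones and initiated by sending a text message with a link to the questionnaires". *Allocation and blinding* shows that staff speak with participants on the calls: "There is a risk that allocation will be revealed to research personnel for some participants during follow-up phone calls". The strengths and limitations list after the abstract says: "Self-report measures will be used which may bias estimates due to social desirability and recall".

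*Limitations* expects attrition to be one of the trial's main weaknesses, concedes that the sequential design gives no protection against systematic missingness, and points to the ancillary attrition analyses and multiple imputation as the response. The article describes no mode term and no within-mode version of the attempts analysis.

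**The concern.** The analysis uses the attempt count as a stand-in for resemblance to people who never answer. That works if the attempt count changes only who answers. Here it also changes how they answer. Early responses come from a form filled in privately; responses at the end of the sequence are collected on a call. Self-reported drinking is the kind of measure for which the two settings may give different answers, and the article itself lists social desirability as a source of bias.

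Two effects then sit on one axis. If late responders drink more but report less on the phone, the association shrinks or vanishes and the analysis reassures wrongly. If phone reports run higher, it overstates the gradient. If there is no gradient, a mode difference alone produces one. Of the missing-data analyses described, this is the one that asks whether observed follow-up drinking varies with how hard a person was to reach, so it should be readable.

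**Working it through.** The article states no figure to reproduce. The check is first structural, then numerical under assumed inputs.

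**Structure.** For a participant who gets every text and does not answer, the sequence is: contact 1, the text with the link; contacts 2 to 4, the reminders ("Up to three reminder texts will be sent at each follow-up interval"); then calls. If the limit of five refers to calls, these are contacts 5 to 9. If it refers to all contacts, there is a single call, contact 5. On either reading no call precedes the texts. Some people who are called may still use the link, so attempt count and mode are strongly, but perhaps not completely, aliased.

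**Assumed inputs (none is in the article).**
- Calls at contacts 5 to 9, all later responses taken by phone, and one follow-up rather than the full multilevel model.
- Three response distributions, with 60%, 75% or 85% of responders answering at the text stage. In the 75% case the shares at contacts 1 to 9 are 0.40, 0.18, 0.10, 0.07, 0.09, 0.06, 0.04, 0.03, 0.03.
- A log-linear gradient with true rate ratio g per attempt, and phone reports multiplied by m.

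**Formula.** If the outcome is regressed on attempts alone, on the log scale,

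observed log slope = ln(g) + b × ln(m),

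where b is the slope of the phone indicator on attempt number. In the 75% case b = 0.1658. With g = 1.05 and m = 0.80: 0.0488 + 0.1658 × (−0.2231) = 0.0118, a rate ratio of 1.012.

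**Results over the three distributions.** The correlation between attempt and phone is 0.86 to 0.88 (variance inflation 3.8 to 4.5). Observed rate ratio per attempt:

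| True ratio | Phone 10% lower | Phone 20% lower | Phone 30% lower |
|---|---|---|---|
| 1.00 | 0.982–0.983 | 0.962–0.964 | 0.940–0.944 |
| 1.03 | 1.011–1.013 | 0.991–0.993 | 0.968–0.972 |
| 1.05 | 1.031–1.032 | 1.010–1.013 | 0.987–0.991 |

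The gradient is cancelled exactly when m = exp(−ln(g)/b): 0.83 to 0.84 for g = 1.03, and 0.74 to 0.76 for g = 1.05.

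In the other direction (75% case), phone reports 20% higher turn 1.03 into exp(0.0296 + 0.1658 × 0.1823) = exp(0.0598) = 1.062, and turn no gradient into exp(0.0302) = 1.031.

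**Simulation and precision.** A negative binomial simulation of the 75% case (1,400 responders, mean 10 at the first contact, dispersion 0.8, 200 replicates, g = 1.05, m = 0.80) gave 1.012 for attempts alone (log-scale SE 0.011) and 1.051 with a phone indicator (SE 0.023). The SE ratio agrees with √4.26 = 2.06. This recovery depends on the assumption that the gradient runs smoothly across the switch.

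For web-completed responses only, the variance of attempt number is 0.995 among 75% of responders, against 5.216 overall. The SE grows by about √(5.216 / (0.75 × 0.995)) = 2.6, to roughly 0.011 × 2.6 = 0.029.

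**The case against.** The strongest reply is about level of detail. The article gives this ancillary analysis one sentence. It does not say that attempts enter as a linear term, that covariates are excluded, or that the result is read alone. If attempts were entered as categories, a step at the first call would be visible. Model form is properly left to an analysis plan that is not shown. That stands as far as it goes. What the article does fix is the attempt count as the proxy and the contact order that ties it to mode; a visible step would still not show whether lateness or mode caused it.

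The reply is also right that no passage says phone and web reports differ. The warning about social desirability covers self-report in general.

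Some stronger readings are tempting, and the article does not support them:
- *The analysis will mask attrition bias.* Only that it can; the direction of any mode effect is unknown.
- *The trial's main results are compromised.* The primary models and the stopping criteria do not use this regression, and comparing available-data with imputed results is a separate check.
- *Possible unblinding on calls distorts the gradient.* That risk is stated for some participants and bears on contrasts between arms, not on the lateness association.
- *Outcomes contradicts Participant timeline.* The former reads naturally as the standard route and the latter as the fallback.
- *The switch comes at one fixed attempt for everyone.* The number of reminders is an upper limit.

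Finally, a mode indicator is not a clean cure. It can absorb a real jump in drinking among phone-stage responders, who are the people most like non-responders.

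**Conclusion.** The point holds in a limited form. The lateness proxy is strongly aliased with collection mode by the trial's own contact schedule, so the planned association cannot be read as a non-response gradient alone. Under the assumed patterns, a phone reporting difference of about 16% cancels a gradient of 1.03 per attempt, and one of about 25% cancels 1.05; differences of the opposite sign exaggerate it. These sizes rest entirely on assumed response distributions, gradients and mode effects. If phone and web reports agree, there is no distortion. The consequence is a weaker ancillary check on missing data, in a trial that expects substantial attrition. It is worth correcting because the correction is cheap.

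**What to change.** - Store the mode (web link or phone) actually used for each follow-up response.
- Keep the planned regression on number of attempts. Beside it, report the attempts association within web-completed responses, and report phone-stage responses as a separate stratum.
- State that a step between web and phone cannot be attributed to lateness or to mode alone. Do not rely on a mode-adjusted slope as the only version.
- Do not add a primary contrast restricted to web-completed responses: it would select on a post-randomisation response variable and discard data.
- Under *Outcomes*, add that non-responders may give data by phone, as *Participant timeline* states. There, make clear whether the limit of five counts calls or all contacts.

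The cost is one stored field and a few sentences of analysis text. The within-mode estimates span a shorter range of lateness and are less precise: under the assumptions above, the web-only slope has about 2.6 times the standard error of the pooled one. If only one call is made, the phone stratum is a single level with no slope of its own.
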